# Protocol for an international multicenter, prospective, observational, non-competitive, study to validate and optimise prediction models of 90-day and 1-year allograft failure after liver transplantation: The global IMPROVEMENT Study

**DOI:** 10.1007/s13304-025-02078-4

**Published:** 2025-03-27

**Keywords:** Liver transplant, Allograft failure, Retransplant, Outcome, Ischemic cholangiopathy, Primary dysfunction

## Abstract

**Graphical Abstract:**

[figure not shown]

**Supplementary Information:**

The online version contains supplementary material available at 10.1007/s13304-025-02078-4.

## Introduction

During the last decade, the expansion of the donor pool using extended criteria (ECD) and donation after cardiocirculatory death donors (DCD) has resulted in heightened attention to allograft failure (AF) due to ischemia–reperfusion injury after liver transplantation (LT). The prompt diagnosis of AF is paramount to defining the indication for early retransplantation. Moreover, the grafts from ECD and DCD may develop early AF during the initial 90 days [1, 2] and delayed AF, primarily due to ischemic cholangiopathy [3]. LT from living donors (LDLT) is a growing procedure worldwide. However, the prevalence of steatosis in the general population is growing, too. A safety threshold for graft steatosis has yet to be entirely investigated, and the possible role of mitigation strategies to reduce the risk of AF in LDLT is a critical unmet need.

The evaluation times and the modalities to promptly identify AF are still the object of research. No consensus exists on the most accurate predictors and indicators of AF, neither on potential mitigation strategies [4–11]. In addition, ECD and DCD grafts are burdened by a higher incidence of ischemic cholangiopathy [12], which typically develops after 6–12 months, which is also a cause of AF and need for retransplantation. With the intent to further expand and optimize the donor pool, machine perfusion (MP) technologies are increasingly employed, allowing utilization of organs that have traditionally been discarded. Moreover, MP allows extended preservation times and assessment of graft viability, especially when considering organs with multiple risk factors (e.g., elderly donors, steatotic grafts, post-anoxic grafts, etc.). [13]

Multiple attempts have been made at evaluating the degree of organ damage and capability to recover function after LT. From the original definition of early allograft dysfunction (EAD) by Olthoff et al. [14, 15], through the model for early allograft function (MEAF) score by Pareja et al. [6] a new category of scores based on the kinetics of multiple parameters have recently emerged. Two scores, one developed in the United States at UCLA (L-GrAFT) [1] and one in Italy from a multicenter cohort (EASE) [2], allow the prediction of early AF with excellent C-statistics. Both were validated on multicentric external populations [16, 17]. L-GrAFT and EASE scores are calculated at day 10 after LT; furthermore, a modification of the L-GrAFT score, calculated at day 7, was subsequently developed and validated [17]. Both scores are also proposed for quantifying the degree of graft recovery in translational studies [18–20]. A synopsis of the characteristics of the different scores is displayed in Table 1. However, the prognostic role of pretransplant graft macrosteatosis, the differences among phenotypic patterns of various transplant types (DBD, DCD, and living donor grafts), as well as the detailed characterization of the dynamics that make retransplantation sustainable or contraindicated have not been investigated [21, 22]. Prospective studies evaluating these endpoints and further mitigation strategies to reduce graft-related risks are still awaited.

**Table 1 Tab1:** Previous scores (object, endpoint, cutoff, number of factors utilized, number of entries, accuracy, discrimination power, strength and limitations)

	DRI (2006) [9]	EAD (2010) [5]	D-MELD (2011) [18]	New ET-DRI (2012) [19]	SOFT (2008) [20]	MEAF (2015) [6]	L-GrAFT (2018) [1]	L-GrAFT (2021) [15]	EASE (2020) [2]
Object of score	Donor quality	Graft quality	Donor–recipient match	Donor quality	Donor–recipient match	Graft recovery	Graft recovery	Graft recovery	Graft recovery
Origin of data	UNOS registry data	3 centers	20 centers	EURO TRANSPLANT registry data	UNOS	Monocentric	1 Center	7 Centers	16 Centers
*N* of patients (developing set)	20,023 1998–2002	297 2004–2005	3281 2002–2009	5723 2003–2007	21,673 2002–2006	1026			
Endpoint	Graft failure	Graft dysfunction	Graft failure/patient death	Graft failure	Patient death	Graft failure	Graft failure	Graft failure	Graft failure
Cutoff and % of predicted at cases	≥ 2 80 % 90 dd	4 75% at 180 dd	Failure: > 1628; 84% at 90 dd Death: > 1628; 86% at 90 dd	> 2 79% at 90 dd	> 40 –	≥ 8 70% at 90 dd	> 1.3 16% at 90 dd	> 1.3 16% at 90 dd	> 0 28% at 90 dd
Evaluation time in relation to LT	Intraoperative (CIT)	7 days	Few hours before LT	intraoperative	Intraoperative CIT	3 dd	10 dd	7 dd	10 dd
Donor	Yes	–	Yes	Yes	Yes	–	–	–	–
Recipient preoperative data	–	–	Yes	–	Yes	–	–	–	Yes
Intraoperative data	–	–	–	–	–	–	–	–	Yes
Transplant logistics	CIT	–	–	Yes	CIT	–	–	–	–
Post-operative data	–	Yes	–	–	–	Yes	Yes	Yes	Yes
Center volume stratification	–	–	–	–	–	–	–	–	yes
Number of variables	8	3	2	8*	19	3	4	4	7*
Total # of determinations	8	3	2	8	19	9	40	27	17
Accuracy at 90 days (derivation set when available)	Not reported	0.72^§^	0.70 and 0.64	0.63	0.69	Not reported	0.85	0.80	0.87
Accuracy at 90 days (validation set or external data set^$^)	0.57^$^	0.63^§$^	0.72 and 0.64	0.58 ^$^	–	0.73 ^$^	0.74	0.74	0.78
Discrimination between highest and lowest risk class					57%	26%			
Strengths	Diffusion		Match oriented		High discrimination	1rst kinetic method	High accuracy high discrimination	High accuracy high discrimination high accuracy in the validation set	High accuracy high discrimination
Limitations	Old, low accuracy, low discrimination		Intermediate accuracy		Intermediate accurac y	Low discrimination	Complexity of calculation (computer)	Complexity of calculation (computer)	Complexity (smartphones/web application) inferior accuracy in the validation set

Abbreviations. $, external data set; §, at 180 days

 Timely prediction of AF is pivotal to identifying patients who may potentially benefit from a rescue retransplant before severe complications develop. When massive cytolysis and clear signs of liver failure occur within the first 2–4 days after LT, the indication for retransplantation is clear. Diversely, the decision to retransplant a patient with a milder degree of AF (also called dysfunction) is more challenging, especially after the first 5–10 postoperative days. AF results from a complex interplay between donor, procurement-related, and recipient perioperative factors, all of which contribute to the severity of the ischemia–reperfusion injury. Conversely, the ability of an allograft to recover from such injury is similarly impacted by numerous perioperative events (e.g., preoperative cardiac ischemic damage, frailty–sarcopenia, graft rejection, drug toxicity, kidney failure, or sepsis), [23–31] many of which are poorly studied. Although L-GrAFT and EASE scores accurately predict AF with excellent discrimination, these existing models have not specifically elucidated the role of perioperative events on the need for retransplantation [1, 2, 17]. Notably, this literature is exclusively based on retrospective, single-center studies which have not considered the center-volume effect, with a limited number of DCD and ECD grafts and no evaluation of the possible mitigation effect of MP technologies [1, 2]. The IMPROVEMENT project was designed to pay particular attention to these shortcomings, to capture and analyze as many of these qualitative and semi-quantitative variables as possible to build a comprehensive model that may meaningfully predict AF and guide treatment decisions regarding retransplantation. The study objectives are detailed in Table 2.

**Table 2 Tab2:** Study objectives

Primary (#1)	To make a snapshot of the liver transplant activity on a global basis
Primary (#2)	To develop new algorithms for the timely prediction of Allograft Failure at 90 and 365 days using a comprehensive prospectively collected dataset based on the current clinical practice of liver transplant centers
Secondary (#3)	To validate the already existing predictive models and the newly developed algorithms on a retrospective cohort of patients from intermediate to high medium-volume transplant centers;
Secondary (#4)	To develop a novel time-based dynamic algorithm, with increasing accuracy from the 3^rd^ to 7^th^ post-operative day;
Secondary (#5)	To identify the best-time for re-transplant (after stratification according to the post-operative weeks, months, trimesters);
Secondary (#6)	To investigate differences in the incidence of allograft failure and ischemic cholangiopathy at 90 and 365 days according to standard DBD, DCD and high- risk DBD, LD donor grafts;
Secondary (#7)	To evaluate the effect of mitigation strategies on the precipitating factors of Allograft Failure at 90 and 365 days;
Secondary (#8)	To investigate the association of kinetic algorithms with development of post- LT complications (acute kidney injury, ischemic cholangiopathy, other complications);
Secondary (#9)	To identify risk factors for mortality that may contraindicate re-transplant;
Secondary (#10)	To investigate the impact of donor-to-recipient gender match on LT outcomes

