### Outcome measures

Allograft failure (AF) was defined as graft failure (leading to retransplant or death) for any reason at day 90 and at day 365 after LT. This definition also captures all late-occurring AFs (also known as delayed non-function) [34, 35] We consider as AF determinants all those events potentially affecting the process of graft function recovery, independently if they were strictly associated with ischemia–reperfusion injury. Indeed, vascular (thrombosis of the hepatic artery or portal vein), biliary, toxic, and major hemodynamic events will be included, because any of them can interact with parenchymal dysfunction, affecting graft function recovery and favoring graft failure and death.

Other outcome measures are comprehensive complication index, intensive care unit length of stay, hospital length of stay (LoS), and cholangiopathy-free survival at 90 and 365 days, graft and patient survival at 90 and 365 days,

The prospective cohort dataset includes 297 data entries and 27 calculated parameters (see supplementary material 1). Variable domains are:identification datadonor characteristics datarecipient preoperative datagraft histology dataintraoperative datarecipient postoperative datastudy endpoints dataoutcome and follow-up data.

The electronic Case Report Form (eCRF) was developed using the REDCap ver 10.0.21 software hosted at https://redcap-irccs.policlinicogemelli.it/. The eCRF allows easy calculation of scores including L-GrAFT and EASE scores.

The REDCAP software performs de-identification and encryption of the data.

The retrospective segment dataset includes 241 variables (supplementary material) to be collected from each center’s previously existing databases.

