#### Study size and power calculations

The study size was calculated to achieve adequate statistical power for the development and validation of prognostic algorithms. Calculations were independently performed by the G-Step Statistical Facility of the Fondazione Policlinico A. Gemelli IRCCS.

*1. Prior knowledge*

1.1. AF incidenceIncidence of allograft failure (AF) at 90 days according to the L-GrAFT study (2018): 11.1% [1].Incidence of AF at 90 days according to the EASE score study: 6.7% [2]—Incidence of EAF according to the L-GrAFT validation study (2020) in UCLA: 7% [17].Incidence of AF at 90 days according to the L-GrAFT validation study (2020) in other US validation centers: 11% [17].Incidence of AF at 90 days according to the L-GrAFT validation study (2020) in European COPE cohort: 4% [17]. Notably, the COPE cohort consists of 222 grafts.

Research hypothesis stratified by donor category:10% AF in liver transplantation with high-risk deceased donors;7% AF in liver transplantation with standard deceased donors;4% AF in liver transplantation with living donors.

1.2. EASE and L-GrAFT score performance as AUC (95% confidence interval)EASE(10) AUC = 0.87 (0.83, 0.91).L-GrAFT10 AUC = 0.72 (0.65, 0.78).L-GrAFT7 AUC = 0.78 (0.75, 0.82).

*2. L-GrAFT and EASE score algorithms validation*

Current target sample size (*n*):5000 transplants overall;> 4125 for the retrospective study.750 for the prospective study.

This estimation aims to provide the minimum sample size to achieve the baseline AUC, considering a different AF incidence for each donor category. The baseline (i.e., lowest) AUC = 0.72 of the L-GrAFT10 score is considered a minimum performance requirement to reach a conservative sample size estimation.

Assuming an overall AF rate of 6% and aiming to exclude an AUC value of 0.72, a minimum sample size of 4000 patients will result in a 95% confidence interval width of 0.072; so, if we obtain an AUC of at least 0.76, the 95% confidence interval, ranging from 0.724 and 0.796, will allow to exclude the value of 0.72.

*3. Dimension of the validation set.*

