Kaplan–Meier curves will be calculated and differences will be investigated through log-rank test.ii.Missing data management.

A. Missing data in the calculation of the area under the curve (AUC) and the slope of the kinetic model will be addressed as follows:Patients who were retransplanted or died before day 10 were excluded from the calculation of the AUC and slope because of the real impossibility to calculate the score which is by definition computed at day 10. The number of this subgroup will be reported in the flow diagram of the patients. These cases will be excluded from the patient population utilized for the development of algorithms. However, these cases will be considered for the calculation of the outcome measures (overall % of AF, % failure at 90 days, % failure at 365 days, length of stay, overall graft survival, and overall patient survival).Patients who have been discharged between day 8 and 10 and do not have the day 10 determination (missing value referring to the day 10 determination of AST or Platelet count or bilirubin). In these cases, the values at day 7 will be used. The number of these cases will be reported in the flow diagram. We are aware that this approach might overestimate the value of the AUC and consequently the score’s value. However, as the number of patients without day-10 data is expected to be small, we believe that the effect will be minimal and not relevant for the purpose of the study.Patients with missing data at day 2, or day 3 will be excluded, being impossible the calculation of the score. Their number will be reported in the flow diagram.Patients with missing data at day 4 will be included. The AUC and the slope will be calculated using the trapezoid method not including day 4. Their number will be reported in the flow diagram.Patients with missing data at day 5 will be included. The AUC and the slope will be calculated using the trapezoid method not including day 5. Their number will be reported in the flow diagram.Patients with missing data at day 6 will be included. The AUC and the slope will be calculated using the trapezoid method not including day 6. Their number will be reported in the flow diagram.Patients with missing data on two consecutive days (day 4 and 5, or day 5 and 6, or day 6 and 7) will be included. The AUC and the slope will be calculated using the trapezoid method not including the two consecutive missing days. Their number will be reported in the flow diagram.Composite missing data (e.g., AST from one day and bilirubin from a different day) will follow the above-mentioned rule. Their number will be reported in the flow diagram.Missing data in the descriptive analysis will be reported. Parameters of interest with percentage of missings higher than 8% will not be reported in tables neither will be considered for further univariate or multivariate analysis.Loss to follow-up.

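### The study size is claimed to give adequate power for developing new algorithms, but both printed calculations size validation only, and the development set is named inconsistently

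*Protocol article*

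**What the plan says.** Study size and power calculations opens with "The study size was calculated to achieve adequate statistical power for the development and validation of prognostic algorithms". Item 2 of that section is headed "L-GrAFT and EASE score algorithms validation". It reads "Assuming an overall AF rate of 6% and aiming to exclude an AUC value of 0.72, a minimum sample size of 4000 patients" and gives the expected result as "if we obtain an AUC of at least 0.76, the 95% confidence interval, ranging from 0.724 and 0.796". Item 3 sizes the validation set by the precision of the O/E ratio: 800 patients at a 6% rate for a standard error of 0.14 on the log scale, with 750 planned.

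Developing new algorithms for failure at 90 and 365 days is primary objective #2. The places that bear on the development data are:

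- **Prospective segment.** Objective #2 refers to a prospectively collected dataset. Table 3 lists new-algorithm development under the prospective segment only. The bias section has high-volume centres build the models and the smaller centres validate them.
- **Whole population.** Setting says the study population is used as a whole for the main algorithms. The Discussion speaks of a new model based on retrospective and prospective data.
- **Validation set.** Item 3 of the size section gives this role to the prospective segment.

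On breadth, the Introduction describes the aim as "to capture and analyze as many of these qualitative and semi-quantitative variables as possible to build a comprehensive model", and Outcome measures states "The prospective cohort dataset includes 297 data entries and 27 calculated parameters". The retrospective dataset has 241 variables.

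**The concern.** A claim of adequate size for model development has to connect the expected events with the number of parameters to be estimated. The article prints its sizing and says that it covers development, but nothing in it makes that connection, and this is a primary objective.

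The consequence depends on which patients are used. With too many candidates for the events, coefficients come out too extreme: predicted risk is too high in high-risk patients and too low in low-risk patients, and the apparent AUC does not reproduce. The Introduction intends the model to guide decisions on retransplantation, so miscalibration at the extremes matters.

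The unclear development set has a second cost. If development is pooled, the retrospective cohort on which objective #3 would validate the new algorithms has already been used to build them.

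**Working it through.** **Step 1. Reproduce the plan's figures.**

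AUC interval, by the Hanley–McNeil standard error. N = 4000 at 6% gives 240 events and 3760 non-events. With A = 0.76, Q1 = A/(2−A) = 0.6129 and Q2 = 2A²/(1+A) = 0.6564.

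SE² = [A(1−A) + 239(Q1−A²) + 3759(Q2−A²)]/(240 × 3760), so SE = 0.01838. The width is 2 × 1.96 × 0.01838 = 0.072, and the interval is 0.724 to 0.796. This matches the plan.

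O/E precision: SE[ln(O/E)] = √((1−p)/(np)). At n = 800 and p = 0.06 it is √(0.94/48) = 0.140, which matches. At the planned 750 it is √(0.94/45) = 0.145. The printed rate interval of 0.043 to 0.077 is the Wald interval at n = 750.

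The inputs are an AUC, a rate and a number of patients. No model-building quantity enters either calculation.

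**Step 2. Expected events at 6%.**

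- Prospective: 750 × 0.06 = 45
- Retrospective: 4200 × 0.06 = 252
- Pooled: 4950 × 0.06 = 297

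Over failure rates of 4% to 10%, the prospective count runs from 30 to 75 and the pooled count from 198 to 495.

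**Step 3. Candidate parameters supported at an expected shrinkage S = 0.90.**

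P = n(S−1) ln(1 − R²/S), where R² is the Cox–Snell value. The documents give no R² for a new model. It is assumed here from an AUC of 0.72 to 0.87 (the lowest and highest score AUCs in the size section) under a binormal linear predictor at 6% prevalence.

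Example at AUC 0.72: 750 × (−0.1) × ln(1 − 0.0368/0.9) = 750 × 0.004175 = 3.1.

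| Assumed AUC | R² | n = 750 | n = 4200 | n = 4950 |
|---|---|---|---|---|
| 0.72 | 0.037 | 3.1 | 17.5 | 20.7 |
| 0.76 | 0.053 | 4.5 | 25.4 | 30.0 |
| 0.80 | 0.073 | 6.4 | 36 | 42 |
| 0.87 | 0.121 | 10.8 | 61 | 71 |

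In whole parameters this is about 3 to 10 on the prospective segment and about 20 to 71 pooled. A second criterion, optimism of at most 0.05 in Nagelkerke R², is less strict and allows about 14 in 750.

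**Step 4. Expected shrinkage for a given number of candidates.**

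S ≈ 1 − P/(P − n ln(1−R²)). For P = 20, n = 750 and AUC 0.76: −750 ln(1 − 0.0529) = 40.8, so S = 1 − 20/60.8 = 0.67.

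| Candidates, n | AUC 0.72 | 0.76 | 0.80 | 0.87 |
|---|---|---|---|---|
| 7, 750 | 0.80 | 0.85 | 0.89 | 0.93 |
| 20, 750 | 0.58 | 0.67 | 0.74 | 0.83 |
| 20, 4950 | 0.90 | 0.93 | 0.95 | 0.97 |
| 50, 4950 | 0.79 | 0.84 | 0.88 | 0.93 |

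**Step 5. Direction of the remaining uncertainty.** Patients retransplanted or dead before day 10 are excluded from algorithm development (Missing data management), which lowers these counts. The 6% is in line with the cited 90-day rates. No 365-day rate is given, but 365-day events are at least as many as 90-day events. The net effect cannot be worked out from the document.

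**The case against.** The strongest reply is that this is a condensed article. The candidate list, any penalisation and internal validation may be in the full protocol or analysis plan. That stands, so their absence is not the finding. The finding is a printed statement about what the size was calculated for, which the printed calculations do not bear out.

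A reader might go further and infer that the new algorithm will be badly overfitted whichever segment is used. The document does not support that, for four reasons:

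- The Introduction sentence on capturing many variables is rationale. It does not say that every variable recorded becomes a candidate. Table 3 names four main parameters, Table 1 lists 4 and 7 variables for the existing kinetic scores, and the 297 entries include identification, endpoint and follow-up fields that cannot be predictors.
- The univariate and multivariate Cox step in the Statistical analysis plan is described for the retransplant time windows, not for the prediction model of objective #2.
- The rule on more than 8% missing values removes variables. It is not evidence of unrestricted selection.
- With pooled data, even 50 candidates at an AUC of 0.80 give an expected shrinkage of 0.88, close to the 0.90 target.

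Pooling is not a complete answer, though. Table 3 marks the post-operative assessment of factors for or against retransplant as not collected retrospectively. Such variables would be absent in 4200/4950 = 85% of pooled patients, so for them only the prospective events count.

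**Conclusion.** The concern holds in limited form. The claim of adequate size for development is unsupported as written, and the document does not say consistently which patients form the development set.

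If development uses the 750, about 45 events support about 3 to 10 candidate parameters. With 20 candidates the expected shrinkage is about 0.6 to 0.8, a high risk of serious overfitting. If development is pooled, about 297 events support about 20 to 71, and a restricted list could be adequate.

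These figures rest on the plan's 6% rate, a shrinkage target of 0.90 and an assumed R². The conclusion for a broad model on the 750 holds over the whole AUC range considered. How many candidates will be used is not fixed in the article, so overfitting is a risk here and not an established result.

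**What to change.** 1. Reword Study size and power calculations so that the size is claimed for validation only, or print a development criterion with its assumed R², shrinkage target and maximum number of candidate parameters.
2. Name one development set and one validation set, and align objectives #2 and #3, Table 3, Setting and item 3 of the size section with them.
3. Before outcome analysis, prespecify the candidate parameters and cap them by the events in the development set after the pre-day-10 exclusion. As a guide before that exclusion, at the plan's AUC of 0.76 the cap is about 4 for the prospective segment and about 30 pooled.
4. Fit the failure-prediction model with penalisation (ridge or elastic net). Report optimism-corrected AUC and calibration slope from a bootstrap that repeats every selection step.

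The cost is a change of wording and routine software. The real downside is that fewer of the recorded variables enter the model, the rest being only described, and that the reported AUC will look less favourable.
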